### Specific aims

The CM intervention is being evaluated by comparing uptake of testing, linkage, and retention in care in 15 communities randomized to either an intervention condition (*n* = 8) or a control condition (*n* = 7) located within the Agincourt HDSS. To measure outcomes in each village, we are linking the longitudinal population-based HDSS data to a health facility-based electronic clinical tracking system used in all HDSS health facilities. The linkage of the health facility and census data allows us to establish an open cohort of approximately 34,000 18–49-year-old residents that includes exposure data (village of residence) as well as outcome data (HIV-related clinical care). Using these data, we will evaluate the effects of the CM intervention by village randomization arm as well as characterize the HIV care cascade in a high prevalence population. We will also evaluate the conceptual model, including the hypothesized CM processes [52], through community surveys to monitor intervention exposure and community level change using validated CM measures [53]. The specific aims of the study include:

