### Community randomization

Communities involved previously in community mobilizing activities (*n* = 12), those not yet fully enumerated in 2014 (*n* = 3), and with fewer than 500 permanent residents (*n* = 1) were not eligible to participate, leaving 15 communities to randomize. In order to achieve a balance among villages on the key covariates at baseline, a restricted or balanced randomization approach [54] was used, taking into account population size, distance to closest health facility, average levels of SES based on household assets [55], temporary migration, female-headed households, and baseline community mobilization scores [53], collected as part of a survey in 2014. Cluster allocation cannot be concealed as CM events and activities are held in public spaces. Further, village leaders were consulted about the trial, consented for their villages to participate, and were present for the allocation. A randomization event was carried out with community representatives. A biostatistician unfamiliar with the area and the villages generated 50 different grouped combinations of intervention and control villages, and these combinations were printed on strips. The assignment was revealed by asking a community volunteer to pick the winning randomization scheme out of a bucket containing all 50 possibilities. The program was then launched in the presence of local leaders and community members.

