Primary analyses will follow an intent-to-treat (ITT) approach and will be unadjusted except for intervention group, and, for longitudinal analyses, time, and the group-by-time interaction. Individual will be the unit of analysis. Our principal interest is to estimate the marginal or population-average effect of the intervention on each outcome rather than the effect for a hypothetical average subject [70]. Moreover, within-subject correlations among outcomes are considered nuisance parameters rather than quantities of interest to be modeled explicitly. Accordingly, generalized estimating equations (GEE) will be used to perform the proposed primary longitudinal analyses, including planned time-averaged comparisons of post-baseline measurements across the intervention and control arms to test primary hypotheses 1–3 listed above. Alpha will be set at .05 for these planned comparisons of each separate outcome. Any additional post-hoc comparisons (e.g., paired comparisons of the control and intervention arms at each time point) will maintain a nominal alpha level of .05 through the use of simulation-based stepdown multiple comparison methods [71]. GEE accounts for correlation of repeated measurements from the same research participant via computation of a working correlation matrix and yields the desired marginal population-average effect estimates [72]. Village ID will be included as a nested fixed effect or via alternating logistic regression (ALR) to account for clustering of persons nested within villages. GEE estimates are consistent even if the correlation structure is mis-specified, though GEE’s statistical efficiency improves as the working correlation structure more closely approximates the actual correlation structure [73]. Thus, several suitable working correlation structures will be considered (e.g., unstructured, AR(1), exchangeable) [74]. The QIC or a similar statistic will be used to select the final working correlation structure [75]. Robust Huber-White “sandwich” standard errors will be used to obtain correct inferences even if the chosen correlation structure remains slightly mis-specified.

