### Power

Minimum detectable differences were calculated according to the methods for proportions in cluster randomized trials proposed by Hayes and Moulton [54], yielding conservative effect size estimates based on clustering by villages. Based on the HDSS data, there are approximately 30,000 adults 18–49 in the study area. We assumed an HIV prevalence of 33% in the adult target population (18–49-year old) [51]. If we conservatively estimate that testing is constant at 35% of the population, at least a third of those tested each year were not tested previously in the study period, and that test positivity is 15% (again a conservative estimate), 449 cases of HIV would be newly identified each year. We further assumed that approximately 50% of individuals who present for CD4 staging would be eligible for HIV treatment under 2014 guidelines. Approximately 6000 individuals were known to be on treatment at clinics in this area in 2014. Our survey data from 2012 suggests that HIV testing in this region exhibits an intra-class correlation of 0.014. In adjustments of power calculations for clustering of outcomes by village, we conservatively assumed an intra-class correlation of 0.05. Table 3 includes outcome estimates for the control proportions based on current literature [18, 26, 27, 68, 79], and the target (intervention) proportions with the minimum increase in proportions that would be detectable as a statistically significant change at alpha of 0.05 and power of 0.80, given the above assumptions. In 2016 (1 year into data collection), the South African government announced universal HIV treatment. This should increase our sample size to assess initiating ART (aim 2) and retention in care (aim 3) in the second and third years of the study.

**Table 3 Tab3:** Power calculations–minimum detectable effects

Outcomes: proportion of population	Current estimate	Intervention group target	Minimum detectable difference (proportion)
Testing; tested in past 12 months	35%	60%	19%
Linkage; undergoing CD4 staging within 3 months of positive test	65%	85%	18%
Linkage; eligible for ART who initiate treatment within 3 months	60%	80%	19%
Retention; HIV positive who remain in care at 12 months	50%	70%	19%

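### The plan relies on Huber-White standard errors for correct inference at alpha .05, but with 15 villages (8 vs 7) and no small-sample correction stated they do not deliver it

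*Protocol article*

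**What the plan says.** The Specific aims section describes "comparing uptake of testing, linkage, and retention in care in 15 communities randomized" to two arms, 8 intervention and 7 control. Under Analysis, "generalized estimating equations (GEE) will be used to perform the proposed primary longitudinal analyses", and "Individual will be the unit of analysis". The primary models are unadjusted apart from arm and, for longitudinal analyses, time and the arm-by-time interaction. The working correlation is described in terms of repeated measurements on one participant. Village is to enter either as a nested fixed effect or through alternating logistic regression.

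On variance, the section says that Huber-White sandwich "standard errors will be used to obtain correct inferences even if the chosen correlation structure remains slightly mis-specified". On the error rate: "Alpha will be set at .05 for these planned comparisons of each separate outcome". No finite-sample variant of the sandwich, no reference distribution and no randomization test is named, and the small number of villages is not discussed there.

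The Power section does treat the village as the source of clustering and uses cluster-trial methods. Under Community randomization, allocation was restricted to balance six village characteristics, and "A biostatistician unfamiliar with the area and the villages generated 50 different grouped combinations of intervention and control villages", one of which was drawn.

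**The concern.** The sandwich variance tolerates a wrong working correlation because it averages the empirical residual variation over many independent clusters. Here the independent units are the villages, and there are only 15. With so few, the plain sandwich is biased downward, because fitted residuals are smaller than true errors. It is also imprecise, so normal limits are too short. The 30,000 or so residents do not help, because the number of villages drives the problem.

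Every primary comparison for aims 1 to 3 uses this machinery. If the true error rate exceeds 5%, a p-value a little below .05 on any aim is open to challenge and the 95% intervals under-cover.

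**Working it through.** **The plan's own figure.** The article gives the nominal alpha of .05 per outcome and no computed error rate. The check is whether the stated method attains .05. Sidedness is not stated; two-sided is assumed.

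**Inputs from the article.** 8 and 7 villages, hence 13 between-village df. ICC 0.014 (observed for testing) and 0.05 (assumed for power). About 30,000 adults, or 2,000 per village. About 6,000 on treatment, or 400 per village. 449 new diagnoses a year, or about 30 per village.

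**Assumption.** The variation in village size is not given, so coefficients of variation (CV) of 0, 0.4 and 0.7 are tried.

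**Equal village sizes, sandwich over villages.** Let the between-village variance of the village summaries be 1.
- True variance of the arm difference: 1/8 + 1/7 = 0.2679.
- Expected uncorrected sandwich: 7/64 + 6/49 = 0.2318.
- Ratio: 0.2318/0.2679 = 0.865. Square root: 0.930, so the standard error is about 7% too small.
- The limit 1.96 then acts as 1.96 × 0.930 = 1.82. On t with 13 df the two-sided tail is 9.1%. Direct simulation (2,000,000 draws) gives 9.2%, or 9.1% in a separate run.
- A t(13) reference alone: 2.160 × 0.930 = 2.01, tail 6.6%.
- Kauermann-Carroll with t(13): expected variance 0.2679, tail 5.0%.
- Mancl-DeRouen with t(13): expected variance 1/7 + 1/6 = 0.3095. The effective limit is 2.160 × √(0.3095/0.2679) = 2.32, tail 3.7%.

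**Beta-binomial simulation of logistic GEE** (20,000 trials per setting, both ICCs, about 15, 30, 400 or 2,000 persons per village):

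| Setting | Uncorrected, 1.96 limit |
|---|---|
| Exchangeable weights, all settings | 8.6–10.1% |
| Independence weights, CV 0.4 | 9.5–10.6% |
| Independence weights, CV 0.7 | 10.9–13.6% |

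In the same settings Mancl-DeRouen with t(13) gives 3.3–4.9%. Kauermann-Carroll with t(13) gives 4.6–6.0%, except under independence weights at CV 0.7, where it reaches 7.1%. In a companion set of simulations, a t-test on village summaries gives 4.9–5.3%.

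**Sandwich over persons only (equal sizes).** The variance is understated by the design effect 1 + (m − 1) × ICC.
- Testing, m = 2,000, ICC 0.014: design effect 28.99, effective limit 1.96/5.38 = 0.364, error 72%. At ICC 0.05: 100.95, 0.195, 85%.
- Retention, m = 400: 45% and 67%.

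**Restricted randomization, then unadjusted analysis** (village-level simulation, six balancing covariates, uncorrected sandwich, 1.96 limit). R² is the share of between-village variance that the covariates explain. The columns are the share of the C(15,8) = 6,435 allocations kept, best balanced first:

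| R² | Best half | Best tenth | Best 1% |
|---|---|---|---|
| 0 | 9.2% | 9.2% | 9.1% |
| 0.1 | 8.9% | 8.2% | 7.6% |
| 0.3 | 7.3% | 6.1% | 5.4% |
| 0.5 | 6.0% | 4.1% | 3.1% |

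**The case against.** Four arguments deserve weight.

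1. **No correction is ruled out.** The corrected estimators are themselves sandwich estimators, the article is a condensed account, and an analysis plan that is not shown could name one. This stands in part: that the sandwich is uncorrected is inferred from the plain estimator being named with nothing added. But the article does choose the estimator and states what it delivers. Followed as written, it gives the wrong error rate, which is more than an omitted detail.

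2. **The sentence speaks only of a misspecified correlation structure.** That is its stated reason, but the robustness it invokes is a many-cluster property, and the promise is made for a trial with 15 clusters.

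3. **The simulated model is simpler than the planned longitudinal one, and the article does not say that the sandwich is taken over villages.** This stands, and it makes the figures conditional. The ambiguity does not favour the plan, because the person-level reading is much worse.

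4. **Balanced allocation with an unadjusted analysis makes tests more conservative.** This stands as a real offset. A reader might infer that each primary test simply runs at about twice its nominal level. The article does not support that as an unconditional statement, because with strongly predictive balancing covariates the error could be near or below 5%. Nor can the plan rely on the offset. The article gives neither how much the covariates explain nor how strictly the 50 schemes were screened: 50 is 0.8% of 6,435, but they may have been sampled from a wider acceptable set.

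**Conclusion.** The concern holds in conditional form. With 8 and 7 villages and nothing further specified, Huber-White errors cannot be said to give correct inference at alpha .05. Taken over villages, uncorrected and with a normal reference, the two-sided error is about 9% with equal sizes or exchangeable weights. It is about 10 to 13% with independence weights at an assumed village-size CV of 0.4 to 0.7. A t reference alone leaves 6.6% at equal sizes.

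These figures assume village-level clustering of the sandwich, a single-period comparison and no benefit from restricted randomization. Such a benefit could remove part or all of the excess, by an amount that cannot be worked out from the article. A person-level sandwich would be far worse for testing and retention. All primary comparisons are affected, so this should be settled before outcomes are analysed.

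**What to change.** State that the sandwich is clustered on village, with a named small-sample correction and a t reference on 13 df. Kauermann-Carroll is close to nominal in most settings tried; Mancl-DeRouen is more conservative. Alternatively, make the primary test a t-test on the 15 village summaries. As a check, add a permutation test over the 50 listed allocations, noting that its smallest p-value is 1/50 = 0.02.

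The cost is one sentence and a software option, with no new data. The loss of precision is not trivial. At equal village sizes, intervals are √(0.2679/0.2318) × 2.160/1.960 = 1.18 times as wide with Kauermann-Carroll, and √(0.3095/0.2318) × 2.160/1.960 = 1.27 times as wide with Mancl-DeRouen. The comparison is with uncorrected intervals that lack their nominal coverage under the conditions above.

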**Fig. 3 Fig3:**
[figure not shown]
Study design and data collection components

To measure coverage of the intervention and changes in the CM domains and other key variables in each community over time, a cross-sectional, population-based survey was administered prior to the intervention and a second survey will take place following the intervention (Fig. 3). The surveys aim to capture 1200 randomly sampled adults, aged 18–49 years, from the HDSS population with approximately 75 people sampled in each of the 15 study villages at both time points. Eligibility criteria for participation in community surveys include residence in the home (spending a majority of nights at home), being 18–49 years of age, and having lived in the study area for at least 9 of the past 12 months. Surveys are interviewer-administered in the participant’s home using computer assisted personal interview (CAPI). Only one individual per household can be selected. Fieldworkers visit the selected homes to confirm eligibility and explain the study. Written informed consent is obtained from all participants prior to the survey; both consent and the survey are offered in the local language, Shangaan, or English. All procedures were approved by the Institutional Review Boards at the University of North Carolina-Chapel Hill and the University of California-San Francisco, the Human Research Ethics Committee (Medical) at the University of the Witwatersrand in South Africa, and the Mpumalanga Department of Health and Social Development Research Committee.

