For hypothesis 4, cross-sectional population data will be collected through representative community surveys. Summary measures of the CM domains before and after the intervention for each village will be calculated from this population representative sample. GEE will be used to model the effects of the pre-post differences in village-level CM domains on individual residents’ HIV testing, and, for HIV-positive individuals, linkage and retention to care using the same overall modeling approach as outlined above. To examine the relative importance of each of the six CM domains, initial models will include the pre-post change scores for each of the six domains in a single model. Subsequent analyses will isolate the marginal effects of each domain via G-computation or other substitution-based estimation strategy [60, 76].

Secondary analyses will extend GEE models to incorporate additional covariates of interest drawn from the HDSS data (e.g., age; gender) and examine their interactions with intervention assignment to ascertain statistical moderation. Secondary analyses will also evaluate whether the pre-intervention/post-intervention village-level difference in the six community mobilization measures mediate the relationships between intervention village residence and the primary outcomes. Statistical mediation will be assessed using the causal inference-based approach of Valeri and VanderWeele, which yields optimal estimates of indirect effects in the presence of binary outcomes and moderator-mediator interactions [77]. M*plus* will be used to implement these mediation analyses because it allows for causal mediation assessment incorporating robust standard errors to address clustering of individuals within villages [78]. Significant indirect and total effects of the intervention on testing, linkage, and retention accompanied by non-significant direct effects will signify mediation in this context.

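### Village mobilization change scores carry survey sampling error for which no allowance is described; one-domain and one-mediator effects would be attenuated, and six-domain coefficients distorted in no fixed direction

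*Protocol article*

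**What the plan says.** **Survey design.** Under Data collection, "a cross-sectional, population-based survey was administered prior to the intervention and a second survey will take place following the intervention". Each round draws a fresh random sample, "with approximately 75 people sampled in each of the 15 study villages at both time points"; no panel is described.

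**Village scores.** Under Analysis (hypothesis 4), "Summary measures of the CM domains before and after the intervention for each village will be calculated from this population representative sample".

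**Association models.** "GEE will be used to model the effects of the pre-post differences in village-level CM domains on individual residents’ HIV testing", and likewise on linkage and retention among HIV-positive residents. "To examine the relative importance of each of the six CM domains", the "initial models will include the pre-post change scores for each of the six domains in a single model". Later analyses then isolate each domain's marginal effect by G-computation or a similar substitution method.

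**Mediation.** The same village-level differences are the mediators in the secondary analyses, fitted in Mplus with robust standard errors for clustering. Mediation is declared when the indirect and total effects are significant and the direct effect is not.

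The article mentions no latent-variable step, shrinkage, regression calibration or other allowance for sampling error in the village scores.

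**The concern.** A village change score has two parts: the true change in the village and the sampling error of two separate means. If the error is of similar size to the true differences between villages, the observed score is a noisy version of the predictor of interest. In a model with one such predictor, its slope shrinks towards zero. In a model with one mediator, the indirect effect shrinks and the direct effect grows by the same amount, so a domain that does transmit the effect can fail both the indirect and the direct part of the plan's rule.

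The large number of residents in the outcome models does not help, because the error sits in 15 village values. Robust standard errors deal with correlated outcomes, not with error in a covariate. The statement under Mediators that the scales performed extremely well concerns the measurement scales, not the precision of a village mean or of a change between two means.

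Identifying the mechanism of the intervention is a stated aim, and the abstract looks forward to validating the mobilization framework. A falsely negative mediation result would count against that framework for the wrong reason.

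**Working it through.** **Inputs.** Respondents per village per round: about 75 (Data collection). Villages: 15. The ICC and pre-post correlation of the mobilization scores are not given. The Power section gives 0.014 (HIV testing, 2012 survey) and 0.05 (planning value for outcomes). These are borrowed as assumptions and the range is extended to 0.10. The correlation *r* of true village means between surveys is assumed to be 0 to 0.7.

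**The plan's own figure.** 75 × 15 = 1,125, against a stated total of 1,200, which needs 80 per village (80 × 15 = 1,200). The gap reflects a loose approximation and does not affect the point; both sizes were run.

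**Reliability of a change score** (respondent SD = 1, *n* per village per round):

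- true variance of change = 2 × ICC × (1 − r)
- sampling variance of change = 2 × (1 − ICC) / n
- reliability = true / (true + sampling)

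Example with ICC 0.05, r 0.5, n 75: 0.05 / (0.05 + 0.0253) = 0.66.

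| ICC | r = 0 | r = 0.5 | r = 0.7 |
|---|---|---|---|
| 0.014 | 0.52 | 0.35 | 0.24 |
| 0.02 | 0.60 | 0.43 | 0.31 |
| 0.05 | 0.80 | 0.66 | 0.54 |
| 0.10 | 0.89 | 0.81 | 0.71 |

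With n = 80 the values at r = 0.5 are 0.36, 0.45, 0.68 and 0.82. A finite-population correction (75 of about 2,000 adults per village, from 30,000 / 15) moves the reliability of a single mean only from 0.516 to 0.525 (ICC 0.014) and from 0.798 to 0.804 (ICC 0.05).

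On the SD scale, the sampling standard error of a change is about 0.16. The true between-village SD of change at r = 0.5 is √0.014 = 0.12 to √0.05 = 0.22. Noise and signal are of the same order.

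**One domain.** The slope is multiplied by the reliability, so the loss runs from 1 − 0.89 = 11% to 1 − 0.24 = 76%. This is exact for a linear model and approximate for a logistic one.

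**One mediator, no interaction.** Let *a* be the effect of arm on the mediator, *b* the effect of the mediator on the outcome, *d* the direct effect and λ the reliability within arm. The estimated indirect effect tends to λab, the direct effect to d + (1 − λ)ab, and the total is unchanged. At r = 0.5, 35% (ICC 0.014) or 66% (ICC 0.05) of the indirect effect is kept, and 65% or 34% moves into the direct effect.

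**Six domains together.** The coefficients tend to (S + E)⁻¹Sβ, with S the true and E the error covariance. Take true effects (1, 0.5, 0, 0, 0, 0), ICC 0.014 and r = 0.5:

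- true correlation 0.5, error correlation 0.3: (0.31, 0.18, 0.04, 0.04, 0.04, 0.04)
- true correlation 0.3, error correlation 0.6: the four null domains become −0.06

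So null domains can move off zero in either direction.

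**Ranking.** A linear village-level regression was simulated with 15 villages, standardized effects (1, 0.5, 0.5, 0.25, 0.25, 0), r = 0.5 and village residual SD 0.5. The strongest domain ranks first in 85% of runs without sampling error, in 28% with it at ICC 0.014 and in 43% at ICC 0.05; chance is 17%. With residual SD 1, it is about 56% even without sampling error.

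**The case against.** **No fixed direction in the joint model.** A reader might infer that every domain effect is biased towards zero. That holds for one-domain and one-mediator models, but not for the six-domain model, nor in general for several mediators or an exposure-mediator interaction. This stands.

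**The ranking is not merely noise.** A reader might also infer that the domain ranking only reflects measurement noise, or orders the domains by how precisely each was sampled. The documents do not support this. All six domains come from the same respondents, nothing shows that their reliabilities differ, and the simulated ranking stays above chance. Six predictors on 15 villages is a large part of the trouble regardless.

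**The size is unknown.** The article gives neither parameter for these scores. In models that omit arm, a real difference in change between arms, as hypothesis 4 predicts, raises reliability: at ICC 0.014 and r = 0.5, from 0.35 to about 0.48 with a 0.2 SD shift and 0.58 with 0.3 SD. This stands for those models, but mediation models condition on arm and gain nothing from it.

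**The article does not call the scores error-free.** A latent or shrinkage step could sit in an analysis plan that is not at hand. Hence the wording that no allowance is described.

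**Correcting the joint model can do harm.** With ICC 0.05 and r = 0.5, a simulated moment correction of the six-domain model left the covariance matrix not positive definite in 75% to 96% of runs. The strongest domain then ranked first in 23% to 28% of runs, against 42% to 50% uncorrected. Stabilising the correction did not rescue it. This stands and limits the remedy.

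**Limited reach.** Aim 4 is worded as exploration and mediation is secondary. Attenuation with one mediator errs towards not claiming mediation. This limits the weight of the point but does not remove it, since a null result would still be interpreted.

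**Conclusion.** The point holds in a limited form. The surveys and models as described use observed village change scores whose sampling error is of the same order as plausible true differences, and no allowance is described. With an ICC of 0.014 to 0.10 and a between-survey correlation of 0 to 0.7, both assumed, one-domain effects and one-mediator indirect effects would lose about 11% to 76%. The lost part of the indirect effect appears as direct effect, so the mediation rule is harder to meet for a true mediator. Joint-model coefficients and ranks are distorted unpredictably, on top of an instability that would exist with perfect scores.

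The documents do not support a claim of general bias towards zero or of a ranking that is nothing but noise, and they do not fix the actual size. The primary comparisons of testing, linkage and retention by arm do not use these scores and are unaffected. This is an inexpensive improvement to aim 4 and the mediation analysis, not a flaw in the trial's main result.

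**What to change.** 1. Report the reliability of each domain's change score, estimated from the individual survey responses.
2. For associations fitted one domain at a time and for single-mediator analyses, give estimates corrected for sampling error beside the raw-mean estimates, for example by regression calibration with each village's survey standard error. In simulation, this brought the median one-domain slope from 35–82% of the truth to about 97–106%. The gain in absolute error of the indirect effect was mixed at ICC 0.05 and above, which is a reason to show both versions.
3. State that, where reliability is low, a non-significant indirect effect or a significant direct effect will not be read as evidence against mediation.
4. Treat the six-domain ranking as exploratory, and do not make a corrected six-domain model the main estimate.

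No new data are needed. The cost is some extra analysis and wider confidence intervals for the corrected estimates.
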